3.2 Sampling type and sample size definition

The sample will be systematic random.

It will be included sequentially patients over 18 years of age with moderate to severe plaque psoriasis with the indication of methotrexate referred by dermatologists to initiate the follow-up in the outpatient clinics of the Hospital of the Federal University of Pernambuco who meet the eligibility criteria and sign the consent form.

The sample size calculation was performed considering the effect of MTX on PASI. The calculation used the formula for comparing paired differences.

To achieve a power of 80 % and a level of significance of 5 % (two-sided) for detecting an effect size of 0,65 between pair was necessary 22 pairs.

For the other variables, the objective was to verify if this effect produced on the PASI would be sufficient to produce a change in them.

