| Place of residence | Urbanization of the place of residence | Interview | 1. Urban zone 2. Rural area |
| Contact with cattle | A person who has worked or had contact for a long time with cattle | Interview | 1. Yes 2. No |
| Nail psoriasis | Presence of pits, onycholysis, splinter hemorrhages, and hyperkeratosis not attributed to another cause in at least one nail. | Physical exam | 1. Yes 2. No |
| Geographical language | Smooth red spots on the tongue | Physical exam | 1. Yes 2. No |
| Psoriasis Scalp | Presence of psoriasis plaques on the scalp | Physical exam | 1. Yes 2. No |
| Palmoplantar psoriasis | Presence of psoriasis plaques on the palms or plants may transgress to the back | Physical exam | 1. Yes 2. No |
| Inverted psoriasis | Presence of psoriasis plaques fold areas | Physical exam | 1. Yes 2. No |
| Enthesitis | Patient presents pain on palpation of entheses without signs of arthritis | Physical exam | 1. Yes 2. No |
| Diabetes | Use of medication for diabetes or two fasting blood glucose levels above 126 mg/dl or an aleatory blood glucose level above 200 mg/dl. | Interview Laboratory tests | 1. Yes 2. No |
| Blood glucose | in mg/ml. | Laboratory tests | average |
| Chest X-ray suggestive of LTBI | Presence of retraction, calcification, hilar or mediastinal lymph node enlargement, or pleural alterations. | Image examination | 1. Yes 2. No |

| Variable | Definition | Method | Categorization |
| --- | --- | --- | --- |
| Treatment maintenance | Defined as patients who achieved 50% or more reduction in PASI score after 12 weeks of treatment and maintained this reduction until the end of the follow-up period. | Physical exam | Sustainer |
|  | Defined as patients who did not achieve a 50% reduction in PASI or those who did but lost response over the follow-up period and need a change in medication. | Physical exam | Non-sustainer |

- 1. Collection techniques
     1. **PASI**

The PASI will be carried out according to the methodology described below:

1) Each body area (head, trunk, upper limbs and lower limbs) will have their percentage of involvement determined by the researcher and will receive a number according the percentage of committed area: 1 < 10%; 2 = 10-29%; 3 = 30-49%; 4 = 50-69%; 5 = 70-89% and 6 = 90-100%

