#### Data analysis plan

The IBM Statistical Package version 23.0 (IBM corp., Armonk, NY) will be used for the statistical calculations.

- Data will be analyzed descriptively through statistical measures: mean ± standard deviation or median and percentiles for numerical variables and absolute and percentage frequencies for categorical variables.
- It will be verified whether there is a significant change in the results of TST and/or IGRA tests, with 2 or 3 categories, classified according to the variables descriptions by the McNemar test. A P < 0,05 will be considered significant.
- It will be verified whether the difference in the comparison of test results is significant before and/ or after treatment by the McNemar test. A P < 0,05 will be considered significant.
- The agreement between each and between the IGRA and the TST before and after treatment, with two or three categories, will be verified by the Cohen’s kappa.
- For numeric continuous variables, the normality will be tested using the Shapiro-Wilk test. To compare the mean of paired continuous variables will be used the Student's t-test for paired variables for variables with a normal distribution, and the Wilcoxon test for variables with a non-normal distribution.
- To compare the TST and IGRA results with the means of numerical continuous variables will be used the Student's t-test for variables with a normal distribution, and the Mann-Whitney test for variables with a non-normal distribution.
- Will be verified the association between the sustainers or non-sustainers status with the categorized variables by the Fisher Exact test. The variables presenting p < 0.05 will be considered a positive association. The variables will be sex, age categorized, duration of illness categorized, alcohol consumption, smoking, presence of other forms of psoriasis associated, blood glucose (normal, diabetic).
- The association between the sustainers or non-sustainers status with the medians/medians of the continuous variables will be verified by t-Student test or Mann-Whitney test, The variables will be the age in years, disease duration in years, BMI, blood glucose in mg/dl, serum levels of INF-γ, TNF-α, interleukin-12, interleukin-17, interleukin-23, ESR, CPR. The association with ESR, CPR, and cytokines will be verified before and after treatment.
- The variables presenting p < 0.05 will be considered a positive association.

.

1. ***Budget****

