**Appendix 6- Laboratory Data Record**

| **LABORATORY DATA RECORD** | |
| --- | --- |
| **Initials** | **Research number** |
| **Birthdate** | **Sex** |

| Test | Result Before MTX | Result After MTX |
| --- | --- | --- |
| QuantiFERON TB-Gold |  |  |
| TNF-alfa in pg/ml |  |  |
| INF-Gama in pg/ml |  |  |
| IL17 in pg/ml |  |  |
| IL 12 in pg/ml |  |  |
| IL23 in pg/ml |  |  |
| CRP in mg/dl |  |  |
| ESR in mm/h |  |  |
| Tuberculin skin test |  |  |

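### The sustainer comparison of after-treatment ESR, CRP and cytokines leaves out each patient's own before-treatment value, which limits what it can show and can cost power (minor)

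*Protocol*

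**What the plan says.** Section 4.2 sets the grouping by outcome. Sustainers are "Defined as patients who achieved 50% or more reduction in PASI score after 12 weeks of treatment and maintained this reduction until the end" of follow-up; the others are non-sustainers.

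The Data analysis plan compares the two groups on numerical variables: the "continuous variables will be verified by t-Student test or Mann-Whitney test". For ESR, CRP (written CPR there), TNF-α, IFN-γ, IL-12, IL-17 and IL-23 it adds "The association with ESR, CPR, and cytokines will be verified before and after treatment". The secondary objectives say the same. The decision rule is "The variables presenting p < 0.05 will be considered a positive association".

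The Laboratory Data Record (Appendix 6) has a column "Result Before MTX" beside an after-MTX column for all seven markers. The one analysis that pairs a patient's marker values is the general rule "To compare the mean of paired continuous variables will be used the Student's t-test for paired variables for variables with a normal distribution", with Wilcoxon as the alternative. It does not mention sustainer status.

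**The concern.** Seven markers at two time points give 14 separate two-group tests, and nothing links the two results for a marker. Sustainer status is not randomised, so nothing balances the markers before MTX, and a difference present at the start may partly persist to week 12. The after-test would then meet the rule for a positive association. That is correct as a statement about levels, but silent on whether the difference arose under treatment. A reader who wants to know whether a marker's response to MTX goes with lasting benefit has no planned analysis to turn to.

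The second cost is precision. Stable variation between patients stays in the error term, although a covariate that could remove part of it is already on the record form.

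**Working it through.** **The plan's own figure.** Section 3.2 states a power of 80% at a two-sided 5% level, "for detecting an effect size of 0,65 between pair was necessary 22 pairs".
- Normal approximation: ((1.960 + 0.842)/0.65)² = 18.6, so 19.
- Exact paired t: 21 pairs (power 80.9%; 82.8% at 22).
- Wilcoxon efficiency 0.955: 21/0.955 = 21.99, so 22.

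The 22 is reproduced. It rests on the effect of MTX on PASI, not on the sustainer comparison.

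**Inputs for the check.** From the protocol: 22 patients, two-sided 5%. Assumed, because the protocol gives neither: the split (11:11, with 15:7 as a variant) and the before-after correlation ρ (0.3 to 0.8). Values are taken as normal, on a log scale if necessary, with SD 1.

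**Step 1: precision.** With the before-value as covariate, the residual variance is (1 − ρ²) times that of the after-value: 0.91 at ρ = 0.3, 0.75 at 0.5, 0.51 at 0.7, 0.36 at 0.8. For a change score the factor is 2(1 − ρ): 1.4, 1.0, 0.6, 0.4. A change score is therefore worse than the planned test below ρ = 0.5.

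The planned t-test with a 1 SD after-treatment difference has noncentrality 1 × √(11 × 11/22) = 2.35 on 20 degrees of freedom, which gives power 0.61 at every ρ. Simulation, with no difference before treatment, 11:11:

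| ρ | Planned after-test | Adjusted for before-value |
|---|---|---|
| 0.3 | 0.61 | 0.62 |
| 0.5 | 0.61 | 0.71 |
| 0.7 | 0.61 | 0.86 |
| 0.8 | 0.61 | 0.95 |

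At 15:7 the planned test has about 0.55 and the adjusted model 0.65 to 0.92 over ρ = 0.5 to 0.8.

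**Step 2: interpretation.** Suppose the groups differ by 1 SD before MTX and MTX adds nothing group-specific. There are two versions. Under common regression on baseline, the difference after treatment is ρ × 1 SD. Under full carry-over, it stays at 1 SD. Share of studies, per marker, 11:11:

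| Version | ρ | After-test p < 0.05 | After significant, before not | Adjusted model p < 0.05 |
|---|---|---|---|---|
| Common regression | 0.5 | 20% | 3% | 5% |
| Common regression | 0.7 | 34% | 4% | 5% |
| Common regression | 0.8 | 44% | 4% | 5% |
| Full carry-over | 0.5 | 60% | 16% | 20% |
| Full carry-over | 0.7 | 61% | 13% | 13% |
| Full carry-over | 0.8 | 61% | 10% | 10% |

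At 15:7 and ρ = 0.5 the misleading pattern under full carry-over reaches 17%. A change score holds 5% under full carry-over but gives 11 to 20% under common regression. No single model is right in both versions.

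**The case against.** The strongest reply is that the plan does what it sets out to do. The secondary objective asks for an association with marker levels before and after treatment, and the analysis tests exactly that. It does not ask about differential response. This stands, and it rules out a stronger reading that a reader might draw from the second table: that the planned after-test produces 20 to 60% false positives. In those scenarios the groups really do differ after treatment, so the test is detecting a true cross-sectional difference. The rates would be errors only if the result were reported as a marker response.

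Second, the before-test on the same marker often shows the earlier difference. This also stands. The pattern that hides it, a significant after-test beside a non-significant before-test, occurs in only 3 to 4% of studies under common regression. The protection is partial: under full carry-over the figure is 10 to 17%, the plan has no rule for reading the two results together, and the before-test restores no power.

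Third, adjustment is not a cure in groups defined by outcome. Under full carry-over the adjusted model is itself significant in 10 to 20% of studies. This stands, and it is why the model should be added beside the planned test and not put in its place.

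Fourth, a log-scale model needs a rule for cytokine values below the assay limits of 2 to 4 pg/ml, whereas Mann-Whitney handles ties directly. This is a fair point about cost.

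An SAP that is not shown could add an adjusted model. The protocol itself, however, already names the test, the time points and the decision rule, and the before-value has no part in them.

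**Conclusion.** The point holds as a minor one about precision and interpretation. The planned after-treatment comparison is valid for the cross-sectional question. It cannot separate a difference that arose under MTX from one carried forward, and no other planned analysis by sustainer status does so. The power loss is material only if the before-after correlation is about 0.5 or more: 0.61 against 0.71 to 0.95 at 0.5 to 0.8, and 0.61 against 0.62 at 0.3. These figures assume 22 patients split 11:11, a 1 SD difference and roughly normal values; the protocol gives neither the split nor the correlation.

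A reader might infer that the planned test is wrong and should be replaced. The documents do not support that, because the stated objective is the association at each time point. Severity is low because the objective is secondary and the sample size was not set for it.

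**What to change.** In the Data analysis plan, keep both planned comparisons and make three additions for the seven markers:

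- Label the after-treatment comparison as cross-sectional and unadjusted.
- Add a linear model of the after-value on sustainer status with the before-value as covariate, on the log scale, or on ranks if the values are skewed or many lie below the assay limit. Report the adjusted difference (a ratio on the log scale) with its 95% interval.
- Base any statement that a marker's response to MTX goes with sustained benefit on that model. Present it as a non-causal association, because the groups are not randomised, are defined by outcome, and adjustment does not fully remove a carried-over difference.

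The cost is one extra model per marker and a rule, fixed before the data are seen, for the choice of scale and for values below the limit. No new samples, visits or patients are needed.

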**Appendix 2 - Clinical Data Record**

| CLINICAL DATA RECORD | | | | | |
| --- | --- | --- | --- | --- | --- |
| Name | | | | Initials: | |
| Birthdate | | | | Research Number | |
| Date of onset of illness: | | | | Sex   1. Male 2. Female | |
| Current Medicine intake: | | | | | |
| BCG scar  Current or less than 6 months use of topical treatment  Previous use of immunosuppressant  Current treatment for psoriasis  Symptoms of active TB  Complete or prophylactic treatment for TB  Laboratory tests with contraindication to methotrexate  In case of yes, describe:  Breastfeeding: | | | 1. Yes 2. No  1. Yes 2. No  1. Yes 2. No  1. Yes 2. No  1. Yes 2. No  1. Yes 2. No  1. Yes 2. No  1. Yes 2. No | | |
| Chest x-ray result description:  Normal 1. Altered 2.  alteration non-LTBI 1. Yes 2. No | | | | | |
| Glycemia in mg/dl |  | Scalp psoriasis | | | 1. Yes 2. No |
| Contact with TB carrier | 1. Yes 2. No | Geographic tongue | | | 1. Yes 2. No |
| Residence place | 1. Urban 2. Rural | Nail psoriasis | | | 1. Yes 2. No |
| Contact with cattle | 1. Yes 2. No | Inverted psoriasis | | | 1. Yes 2. No |
| Alcohol intake | 1. Yes 2. No | Palmoplantar psoriasis | | | 1. Yes 2. No |
| Smoking | 1. Yes 2. No | Enthesitis | | | 1. Yes 2. No |
| Diabetes | 1. Yes 2. No | Scalp psoriasis | | | 1. Yes 2. No |

**Appendix 3- Standardized questionnaire for screening for tuberculosis**

| **Initials** | | **Research number** |
| --- | --- | --- |
| **The patient has presented some symptom compatible with TB:** | | |
| 1 | Productive cough for more than 3 weeks | 1. Yes 2. No |
| 2 | Hemoptysis | 1. Yes 2. No |
| 3 | Asthenia | 1. Yes 2. No |
| 4 | Fever | 1. Yes 2. No |
| 5 | Night sweats | 1. Yes 2. No |
| 6 | Anorexia | 1. Yes 2. No |
| 7 | Weight loss over 10% of ideal weight | 1. Yes 2. No |
| If any of the above answers were positive, active TB needs to be completely discarded. | | |
| **The patient has presented other risk factors for TBLI** | | |
| 8 | Diabetes | 1. Yes 2. No |
| 9 | Illicit drug use | 1. Yes 2. No |
| 10 | Born in an endemic area for TB | 1. Yes |
| 11 | History of previous treatment for TB | 1. Yes 2. No |
| 12 | History of previous prophylaxis for TB | 1. Yes 2. No |
| 13 | Family history of TB |  |
| A | Parents | 1. Yes 2. No |
| B | Grandparents | 1. Yes 2. No |
| C | Partner | 1. Yes 2. No |
| D | Child | 1. Yes 2. No |
| E | Own patient | 1. Yes 2. No |
| 14 | Recent contact with TB carrier | 1. Yes 2. No |
| 15 | Live or work in a high-risk environment | 1. Yes 2. No |

**Appendix 4 - Laboratory Follow-up Record**

| **Flowchart of laboratory exams** | | | | | | | | | | | |
| --- | --- | --- | --- | --- | --- | --- | --- | --- | --- | --- | --- |
| **Initials** | | | | | | | **Research number** | | | |  |
| **DATE** |  |  |  |  |  |  |  |  |  |  |  |
| **HB** |  |  |  |  |  |  |  |  |  |  |  |
| **HT** |  |  |  |  |  |  |  |  |  |  |  |
| **VCM** |  |  |  |  |  |  |  |  |  |  |  |
| **HCM** |  |  |  |  |  |  |  |  |  |  |  |
| **LEUCO** |  |  |  |  |  |  |  |  |  |  |  |
| **SEG** |  |  |  |  |  |  |  |  |  |  |  |
| **INF** |  |  |  |  |  |  |  |  |  |  |  |
| **EOS** |  |  |  |  |  |  |  |  |  |  |  |
| **MONO** |  |  |  |  |  |  |  |  |  |  |  |
| **PLT** |  |  |  |  |  |  |  |  |  |  |  |
| **UREIA** |  |  |  |  |  |  |  |  |  |  |  |
| **CREA** |  |  |  |  |  |  |  |  |  |  |  |
| **AST** |  |  |  |  |  |  |  |  |  |  |  |
| **ALT** |  |  |  |  |  |  |  |  |  |  |  |
| **FALC** |  |  |  |  |  |  |  |  |  |  |  |
| **GGT** |  |  |  |  |  |  |  |  |  |  |  |
| **Total cholesterol** |  |  |  |  |  |  |  |  |  |  |  |
| **HDL** |  |  |  |  |  |  |  |  |  |  |  |
| **LDL** |  |  |  |  |  |  |  |  |  |  |  |
| **VLDL** |  |  |  |  |  |  |  |  |  |  |  |
| **TRIGLI** |  |  |  |  |  |  |  |  |  |  |  |
| **GLI** |  |  |  |  |  |  |  |  |  |  |  |
| **ESR** |  |  |  |  |  |  |  |  |  |  |  |
| **CPR** |  |  |  |  |  |  |  |  |  |  |  |
| **Serologies** |  |  |  |  |  |  |  |  |  |  |  |
| **Others** |  |  |  |  |  |  |  |  |  |  |  |
| **Medication** |  |  |  |  |  |  |  |  |  |  |  |

**Appendix 5 – PASI SCORE CALCULATION**

| PASI | | | | |
| --- | --- | --- | --- | --- |
| Initials | | | Research number | |
|  | Head | | Arms | |
| Area in% |  0  <10   10-20  30-49    50-69  70-89 90-100 | |  0 <10   10-20 30-49    50-69  70-89 90-100 | |
| Erythema | 0 1 2 3 4 | | 0 1 2 3 4 | |
| Thickness | 0 1 2 3 4 | | 0 1 2 3 4 | |
| Desquamation | 0 1 2 3 4 | | 0 1 2 3 4 | |
|  | Trunk | | Legs | |
| Area in% |  0  <10   10-20  30-49    50-69  70-89 90-100 | | 0 <10   10-20 30-49   50-69 70-8990-100 | |
| Erythema | 0 1 2 3 4 | | 0 1 2 3 4 | |
| Thickness | 0 1 2 3 4 | | 0 1 2 3 4 | |
| Desquamation | 0 1 2 3 4 | | 0 1 2 3 4 | |
|  | Head x 0,1 |  | Arms x 0,3 |  |
|  | Trunk x 0,3 |  | Legs x 0,4 |  |
| Total |  | |  | |

**Appendix 6- Laboratory Data Record**

| **LABORATORY DATA RECORD** | |
| --- | --- |
| **Initials** | **Research number** |
| **Birthdate** | **Sex** |

| Test | Result Before MTX | Result After MTX |
| --- | --- | --- |
| QuantiFERON TB-Gold |  |  |
| TNF-alfa in pg/ml |  |  |
| INF-Gama in pg/ml |  |  |
| IL17 in pg/ml |  |  |
| IL 12 in pg/ml |  |  |
| IL23 in pg/ml |  |  |
| CRP in mg/dl |  |  |
| ESR in mm/h |  |  |
| Tuberculin skin test |  |  |

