**TST reading visit one**

1. The patient will be scheduled to read the result of the TST in 72 hours. The TST reading will be performed by *[name]*. The results will be photographed for archiving and noted in the laboratory data record. (Appendix 6).
2. The main research will provide the MTX prescription. The patients will be instructed to take 3 cp of 2.5 mg of MTX twice in a single day of the week, for a total dose of 15 mg per week without dose progression. Patients should start the medication the next day to avoid errors. They will be instructed to intake 5 mg of folic acid once a week in the day after the use of MTX.
3. Patients will reevaluated 30 days after starting medication to assess adverse effects. In case of adverse effects, they should attend the consultation before the deadline. Patients who discontinued the medication or skipped doses for any reason before the second visit were excluded.
4. The patient will be scheduled with one month and with tree months, before visit two, to verify the adherence to methotrexate and perform blood count, liver enzymes, renal function, and pregnancy test for women. The CPR and ESR levels will be reassessed only in three months. In case of a change in the exams or if the patient stops MTX, they will be excluded.

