**TST reading visit two**

1. The patient will be scheduled to read the result of the TST in 72 hours. The TST reading will be performed by *[name]* as the same as visit 1.

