4.2 Variables definition

| Variable | Definition | Categorization |
| --- | --- | --- |
| ***TB screening*** | |  |
| **Quantiferon TB- gold first categorization** | Tests classified as positive by the manufacturer | 1. Positive |
|  | Tests classified as positive by the manufacturer | 1. Indeterminate |
|  | Tests classified as positive by the manufacturer | 1. Negative |
| **QuantiFERON TB-gold second categorization** | Tests classified as positive or undetermined | 1. Positive |
|  | Tests classified as negative | 1. Negative |
| **TST first categorization** | <5 mm | 1. Negative |
|  | 5 mm ≤ TST < 10 mm | 1. Indeterminate |
|  | ≥ 10 mm | 1. Positive |
| **TST second categorization** | <5 mm | 1. Negative |
|  | ≥ 5 mm | 1. Positive |

| *Cytokines* | |  |
| --- | --- | --- |
| **TNF-α** | in pg/ml | Average |
| **IFN-γ** | in pg/ml | Average |
| **IL -12** | in pg/ml | Average |
| **IL- 17** | in pg/ml | Average |
| **IL-23** | in pg/ml | Average |
| ***Inflammatory markers*** | |  |
| **CRP** | in mg/l | 1. ≤ 1 2. > 1 |
|  |  | Average |
| **ESR** | in mm/h | 1. ≤10 2. >10 |
|  |  | Average |
| ***Clinic*** |  |  |
| **PASI absolute** | psoriasis severity index calculated as described in methods | Mean/median |
| **PASI reduction** | Percentage reduction of PASI after the use of methotrexate | 1. <50% 2. 51-74% 3. > 75 %   Média/mediana |

| Variable | Definition | Method | Categorization |
| --- | --- | --- | --- |
| Sex | Biological gender of the patient | Interview | 1. Male 2. Female |
| Age | The time between the date of birth and study interview day, in full years | Identification document | 1. *18 ≥ x* < *30* 2. *30 ≥ x < 60* 3. *≥ 60*   Average |
| Disease duration | Estimated time between the age of onset of illness and the age at study interview day in full years | Interview | 1. < 2 year 2. 2 *≥ x <* 10 years 3. *≥ 10*  years   Average |
| alcohol intake | Have consumed more than one dose per day if the patient is a woman or 2 doses if is a man in the last 30 days. | Interview | 1. Yes 2. No |
| Smoking | I have smoked for more than one day in the last 30 days. | Interview | 1. Yes 2. No |
| Contact with Tb carrier | Characterized by a family history of TB (parents, uncles, grandparents, partners, children or own patient), know someone with TB as a neighbor, friends, co-workers or works in a high-risk TB environment | standardized questionnaire | 1. Yes 2. No |

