**4.3.4 Tuberculin Skin Test**

The tuberculin test will be performed by the intradermal application of 2 UT of purified protein derivative (PPD Rt 23) preferably on the inner surface of the left forearm at the first visit and preferably at the right at the second visit. If there is a psoriasis lesion at the site of application, the arms may be inverted. The results will be read after 72 hours and recorded in millimeters.

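### Nothing masks the visit-two TST reading to the visit-one value, and both go on one before/after sheet, so the TST change and its before/after kappa may be biased

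*Protocol*

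**What the plan says.** All references are to the protocol.

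- Section 4.3.4 makes the TST a manual measurement: "The results will be read after 72 hours and recorded in millimeters".
- Collection protocol, TST reading visit one, item 1: the result is photographed for the archive and "noted in the laboratory data record", which is Appendix 6.
- TST reading visit two: the reading is done "as the same as visit 1". No other instruction about the second reading is given.
- Appendix 6 is one sheet per patient with the columns "Result Before MTX | Result After MTX" and a row labelled "Tuberculin skin test".
- Section 4.2 cuts the reading at 5 and 10 mm. The middle category is "5 mm ≤ TST < 10 mm".
- The main objective includes the change in TST results under MTX, and the specific objectives include TST agreement. The data analysis plan uses McNemar and Cohen's kappa for these.
- The study design section describes a single-arm study in which patients are their own controls.

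No section describes masking the second reading to the first, an independent second reader, or a masked re-reading of the photographs.

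**The concern.** The TST effect is the difference between two readings that depend on a person's judgement. There is no control arm, so anything that acts on the second reading and not on the first is counted as an MTX effect, or hides one.

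If the procedure is followed as written, the second millimetre value goes in the cell next to the first, under a heading that names the treatment period. Whoever completes the form can see the earlier number. Two things could follow:

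- The second reading is drawn toward the first. The change shrinks and before/after agreement, itself an objective, looks better than it is.
- The second reading is drawn toward the suppression that the reader expects. The change grows.

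The other main test is better protected. Section 4.3.3 runs the QuantiFERON ELISA only after inclusion has ended, in duplicate, with software interpretation. The skin test, the more subjective of the two, has no comparable safeguard.

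**Working it through.** **Step 1: what the sections establish together.** The visit-one text sends the reading to Appendix 6. The visit-two text repeats the visit-one procedure. Appendix 6 holds both values on one page. So both readings end up side by side, and no instruction withholds the first from the second reader.

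**Step 2: what they leave open.** They do not say who writes on the form, whether it is present at the second reading, or whether the first value is looked at. The reader's name is removed, and the visit-two wording can mean the same person or the same manner.

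**Step 3: size, as an illustration only.** The protocol has no figure on reading error or anchoring, so there is nothing of its own to reproduce. Its 22 pairs were sized on PASI (effect size 0.65), not on TST.

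Assumed inputs: half of 22 patients react, with mean 10 mm and SD 4; MTX changes the reaction by -2 mm on average, SD 2; reading error SD 1 mm. Let w be the pull toward the first value:

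recorded reading 2 = w × reading 1 + (1 - w) × independent reading 2

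Subtracting reading 1 gives:

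recorded change = (1 - w) × independent change

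In simulation (400,000 draws) the mean independent change in reactors is -1.95 mm; reactions cannot fall below 0 mm, so it is slightly smaller than -2. Then:

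- w = 0: -1.95 mm
- w = 0.25: 0.75 × (-1.95) = -1.46 mm
- w = 0.50: 0.50 × (-1.95) = about -0.97 mm

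The proportional loss equals w whatever the true change is. Only w is unknown.

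**Step 4: categories.** Under the same inputs, the expected positive-to-negative changes per 22 patients are:

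| Cut | w = 0 | w = 0.25 | w = 0.50 |
| --- | --- | --- | --- |
| 10 mm | about 2.2 | about 1.7 | about 1.2 |
| 5 mm | about 1.7 | about 1.2 | about 0.7 |

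Fewer recorded changes mean higher before/after agreement, hence a higher kappa.

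**Step 5: does this decide McNemar?** With all discordant pairs in one direction, the exact two-sided p is 2 × 0.5^m. Five pairs give 0.0625 and six give 0.031, so at least six are needed. With about two expected, power under these inputs is only about 1.3% (10 mm) and 0.5% (5 mm) with no anchoring at all. The test decision is almost always the same with or without it.

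A larger assumed effect behaves differently. If 30% of patients truly turn negative and 5% positive, power is about 0.38; hiding 25% or 50% of those changes lowers it to about 0.21 or 0.07. The protocol gives no expected TST change, so neither scenario can be preferred and no claim about McNemar is made.

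**The case against.** The strongest reply is that a form's layout is not a reading procedure. Appendix 6 also collects the QuantiFERON and cytokine results, which are assayed only after inclusion ends, so it may be a summary sheet filled in over time by someone other than the reader. That is possible. It means exposure to the first value is likely rather than stated. It does not supply masking, because no other recording step for the TST is described.

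A reader might infer three stronger things, none of which the protocol supports:

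- *That the MTX effect on TST is biased.* Only the opportunity for bias is shown. Size is unknown, and the direction could be either way.
- *That the same person reads both tests, and that this is a fault.* The wording is ambiguous. One reader would in any case limit between-reader variation.
- *That losing one or two discordant pairs decides the McNemar result.* Steps 4 and 5 show that this does not follow. In the illustration the loss at the 10 mm cut is about 0.4 to 1.0 changes, in a test with almost no power to begin with.

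Some features soften the risk. The test is placed "preferably on the inner surface of the left forearm at the first visit and preferably at the right at the second visit", the readings are about 12 weeks apart, and at least the visit-one result is photographed. None of these hides the earlier number or the time point, and no re-reading of the photographs is planned.

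Nor is this a matter for an analysis plan. What the reader can see is fixed by the collection procedure and its forms, and an anchored reading cannot be corrected afterwards.

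**Conclusion.** The point holds as an avoidable risk of observer bias, not as a demonstrated bias. The second TST reading is not masked to the first, and the record form places the two values side by side, in an uncontrolled study whose main objective includes this comparison. The quantities exposed are the estimated TST change and the before/after kappa.

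If the only mechanism is a pull toward the first value, the mean change is understated by the fraction of the pull (a quarter or a half in the illustration) and kappa is inflated. Both the pull and the reaction sizes are assumptions. Expectation of suppression would act in the opposite direction and has not been modelled. The remedy is worth making because it costs little, not because the harm is known to be large.

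**What to change.** - Replace the two-column TST entry in Appendix 6 with separate single-visit sheets, identified by research number and without before/after columns.
- File the visit-one sheet and photograph after visit one, so that neither is available at the visit-two reading.
- Under TST reading visit two, add one sentence: the second millimetre value is measured and signed before any access to the first.
- Join the two sheets only at data entry.

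The same reader may be kept. The cost is one redesigned form, one sentence and slightly more form handling, with no extra staff or visits and no change to the sample size.

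The fix is partial. The reader will still know that the second reading follows MTX, and may remember some patients. That limitation should be stated when the results are reported.
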